## Abstract

**Introduction:**

Limb motor dysfunction is one of the challenges in rehabilitation after cerebral ischemic stroke (CIS) and greatly affects the quality of life of patients. This study aims to investigate the central mechanisms of the curative effect with multimodal magnetic resonance imaging (MRI), which will provide additional evidence to support the application of Xingnao Kaiqiao (XNKQ) acupuncture.

**Methods and analysis:**

This trial is a randomized controlled trial. Patients who meet the criteria will be recruited and randomly divided into 2 groups. One group will receive acupuncture treatment and another group will not receive acupuncture treatment. Both groups will receive conventional treatment. In addition, 20 healthy individuals will be recruited who will not receive any treatment. The total course of treatment is 14 days. The primary outcome is multimodal MRI analysis. For safety assessment, adverse events will be observed and recorded.

**Ethics and dissemination:**

The study involving human subjects was reviewed and approved by the Ethics Committee of IRB of The First Teaching Hospital of Tianjin University of TCM (TYLL2023[K]031). This study complied with the Declaration of Helsinki. Written informed consent about this study was provided by the participants. The results of this study will be published in a peer-reviewed journal.

**Clinical trial registration:**

Chinese Clinical Trial Registration Center (ChiCTR2300078315) https://www.chictr.org.cn/.

## Introduction

Data (1) from the Global Burden of Disease study show that the absolute number of stroke episodes increased by 70.0% from 1990 to 2019, while the age-standardized rates of stroke incidence decreased by 17.0%. Stroke (2) is the leading cause of disability and death in adults in China. By 2019, the number of stroke patients in China was about 28.76 million (3), of which cerebral infarction accounted for 24.18 million. If it is not treated and prevented in time, cerebral ischemic stroke (CIS) patients will be disabled or even have a recurrence of cerebral infarction in a short period, which will seriously affect their life and health and increase their economic burden.

About 12.5% of stroke survivors left with a disability in 2020 (2), equivalent to file.2 million people. After 12 months of follow-up, the rate of disability among stroke survivors was 14.8% at 3 months and 14.0% at 12 months. Therefore, how to effectively improve limb dysfunction and help patients return to daily life still needs to be further explored. In this process, exploring the brain’s mechanistic changes to improve treatment options can provide better help to patients.

Functional magnetic resonance imaging (fMRI) (4) is a non-invasive and radiation-free imaging technique, and multiple sequences can show different brain functional changes, which is widely used to study brain mechanisms (5). It can monitor the activation of brain regions, and brain functional connectivity, guide clinical rehabilitation and suggest patient prognosis.

Acupuncture is a traditional Chinese medicine treatment technique that is applied to a variety of diseases. Xingnao Kaiqiao (XNKQ) acupuncture was founded by academician [name] of Tianjin University of Traditional Chinese Medicine. Its clinical effects have been satisfactorily verified. It is now widely used in post-stroke rehabilitation. And clinical data show its safety and efficacy. Further research is needed to support the mechanism by which XNKQ acupuncture acts on the brain in CIS patients. We used multimodal MRI technology to further explore the central mechanism by which XNKQ acupuncture exerts action in patients with post-stroke limb dysfunction.

## Methods and analyses

### Design and setting

This is the version of the protocol, dated 1 April 2023. The study protocol was designed in accordance with standard protocol Items: Recommendations for Interventional Trials (6) (Supplementary File 1). The study protocol was approved by the Ethics Committee of IRB of The First Teaching Hospital of Tianjin University of TCM (TYLL2023[K]031). The study will be conducted in the First Teaching Hospital of Tianjin University of Traditional Chinese Medicine. In this study, 40 patients with post-stroke limb dysfunction and 20 healthy people will be included, and patients will be randomized into 2 groups in 1:1 ratio. The intervention group will receive XNKQ acupuncture therapy and basic therapy, the control group only will receive basic therapy. Acupuncture treatment will be given 6 times a week for 2 weeks. Outcome indicators include clinical scales and imaging indicators. Healthy people will be accessed at baseline, patients will be evaluated at baseline and after 2 weeks. The flow chart of this study is shown in Figure 1. The schedules of this study is shown in Table 1.

**Figure 1 fig1:**
[figure not shown]
Flow chart of the trail.

**Table 1 tab1:** Schedule of the trial.

Time point	Study period			
	Enrollment-1 week	Allocation 0 week	Baseline 0 week	Treatment phase 2 weeks
Enrollment				
Eligibility screen	√			
Demographic	√			
Characteristics				
Informed consent	√			
Medical history	√			
Merger disease	√			
Randomization		√		
Intervention				
XNKQ group		√		
Control group		√		
Healthy People				
Assessment				
FMA			√	√
NIHSS			√	√
mRS			√	√
MBI			√	√
EQ-5D			√	√
Imaging data			√	√
Adverse event				√

### Recruitment and informed consent

Recruitment information will be available to patients in the form of posters at various locations in the hospital, and interested patients can contact the program leader by phone and e-mail. Eligible patients must meet the inclusion and exclusion criteria. If an applicant meets the study criteria, they will be invited to participate and sign written informed consent before the start of the study (Supplementary File 2). The following basic personal information will be collected: sex, age, height, weight, educational background, occupation, marital status, health insurance and related past health history, etc. These details of the participants will be for the record only and will never be revealed to any individual or organization not connected to the study.

### Diagnostic criteria

The diagnostic criteria are as follows: Refer to the diagnostic criteria for CIS in Chinese Guidelines for Diagnosis and Treatment of Acute Ischemic Stroke in 2018, all patients had acute onset and neurological deficits lasting more than 24 h. Imaging showed the presence of infarct lesions and ruled out non-vascular causes.

### Inclusion criteria

The inclusion criteria are as follows:

1. Patients group:Meets the above diagnostic criteria;First-ever clinical CIS occurred ≤2 weeks, the number of times ≤ 1;40–70 years old, right-handed;Unilateral basal ganglia infarction and the area of infarction is 3.0 ~ 5.0 cm in diameter at the largest level, with motor dysfunction and manual muscle testing showing muscle strength grades 1 to 4;No severe cognitive impairment and also mini-mental state examination (MMSE) with a score of 17 or above.Provided written informed consent to participate.

2. Healthy people groupAge and sex were matched with the patient group, right-handed;Subjects are in good health and free of organic and significant functional diseases;No previous family history of the mental and nervous system;No stimulant drugs have been taken in the past 2 months;Provided written informed consent to participate.

### Exclusion criteria

The exclusion criteria are as follows:Patients with a history of stroke, or diseases such as brain tumors or rheumatoid arthritis that result in an mRS Score of ≥2;Patients with severe heart, liver, kidney, blood system, endocrine system, and mental illness, or with other diseases that prevent them from cooperating with treatment;Patients with a history of metal implants in the past or with claustrophobia who are not able to finish in the MRI scanning room;Persons with hearing and vision disorders that obstruct communication;Pregnant and lactating women;Currently participating or have participated in other clinical studies that have not yet been completed for more than 3 months.

### Removed criteria

Patients will be removed if they have:Patients with poor compliance during clinical trials who voluntarily withdrew from the study;Patients are not appropriate to continue the research who are with serious adverse reactions, serious complications, or deterioration of condition that occurred in the study;The subjects did not complete the tasks as required (less than 50% percent of the tasks or receiving treatment of other trials) or had incomplete image observation data.

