### Acupuncture group

Acupoints of XNKQ acupuncture included bilateral PC6, DU26, and affected side SP6. Patients will be in the supine position. Acupoints will be sterilized with 75% alcohol before acupuncture. The first acupuncture point to be needled will be PC6, then the needle body will be rotated to stimulate the acupoints with a speed of 40-60/min and a rotation angle of more than 180°. The second will be DU26, the needle body will be rotated 360° and fixed to the skin, and moved to stimulate the acupoint until the eye is moist or weeping. Finally, SP6 will be stimulated until the leg twitches 3 times.

Depending on each patient’s tolerance level, the therapist adjusts the acupuncture strength until the patient achieves “deqi” without significant pain. Leave the needle in place for 30 min per treatment. Acupuncture 6 times per week for 2 weeks for a total of 12 times.

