### Non-acupuncture group

In the non-acupuncture group, patients will receive the same basic treatments as the acupuncture group except for acupuncture.

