### Data collection and statistical analysis

Data will be collected using the paper CRFs which will be kept in a locked cabinet at the end of the trial. Statistical analysis of data will be performed by an independent researcher. For dislocated subjects, we will record the number and reason for termination, especially adverse events. Data will be analyzed using the R software version R-4.2.2. Statistical significance is defined as a *p* value of <0.05.

For comparisons of baseline material, measurements that follow a normal distribution overall will be expressed as mean ± standard deviation (
$\bar{X}$
 ± SD), and the whole data that do not follow a normal distribution will be expressed as median (interquartile range, IQR) [M (P25-P75)]. Count data will be expressed as the number of cases (n) and percentage (%) using the X^2^ test. The *t*-test or Mann–Whitney U-test will be chosen to compare the two groups’ scores on each scale based on a normal distribution and homogeneous variance. For within-group comparisons, changes in scores will be assessed by paired *t*-test or Wilcoxon rank-sum test. For subjects who discontinued or deviated from the intervention, listwise deletion or multiple interpolation will be used.

The multimodal MRI images will be analyzed by MATLAB 2023a and the statistical parameter graph software Statistical Parametric Mapping (SPM)12. Before data processing, all data will be removed the first 10 time points to retain the stabilized images; and adjust for differences arising from the time points, after which orientation alignment will be performed; and all aligned functional images will be aligned to the montreal neurological institute (MNI) space with a voxel standard size of 3 mm × 3 mm × 3 mm, and then the functional images will be smoothed with a Gaussian kernel of 6 mm × 6 mm × 6 mm. Afterward, the images will be datamined by extracting the indicators. Data will be analyzed with two independent samples *t*-tests to compare the differences between the patient group before treatment and the healthy group, as well as the differences between the acupuncture group and the no-acupuncture group after treatment. The longitudinal changes in MRI indexes before and after the respective treatments of the two groups of patients will be observed with paired *t*-tests. Age, gender, BMI, blood pressure, and history of diabetes will be used as covariates in data analysis.

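### Randomised patients can be removed or deleted for events after allocation that are tied to outcome or treatment, so the arms compared need not be the arms randomised; the direction of bias is unknown

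*Protocol article*

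**What the plan says.** Protocol article, Removed criteria, lists who is taken out of the study after enrolment:

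- Non-compliance: "Patients with poor compliance during clinical trials who voluntarily withdrew from the study".
- Patients judged unsuitable to go on because of "serious adverse reactions, serious complications, or deterioration of condition that occurred in the study".
- Completion and other-trial treatment: "The subjects did not complete the tasks as required (less than 50% percent of the tasks or receiving treatment of other trials".
- Imaging: "or had incomplete image observation data". MRI is the primary outcome.

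Data collection and statistical analysis adds: "For subjects who discontinued or deviated from the intervention, listwise deletion or multiple interpolation will be used". I read the last method named there as multiple imputation. The same section says the number of patients who stop and their reasons will be recorded.

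Design and setting states that "patients will be randomized into 2 groups in 1:1 ratio". Only the acupuncture arm has a course of sessions: "Acupuncture 6 times per week for 2 weeks for a total of 12 times". In the other arm "patients will receive the same basic treatments as the acupuncture group except for acupuncture".

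Nowhere does the article say that removed patients are still followed up or analysed in their allocated arm.

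**The concern.** Randomisation protects a comparison only while the patients analysed are those allocated, or are lost for reasons unrelated to outcome and arm. Here several reasons for removal are related to one or both. Worsening of the condition is close to what NIHSS, FMA, mRS and MBI measure. Serious reactions and low completion can depend on the treatment received. Incomplete images are missing data on the primary outcome, so that clause amounts to a complete-case rule for it.

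The analysis section adds a second problem. Its trigger is stopping or departing from the intervention, not the absence of a value. Under the deletion option, a patient who missed sessions but attended the week-2 assessment could have observed data discarded. Whether deletion or imputation is used is left open and could be settled after the data are seen.

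At stake is the post-treatment comparison of the two patient arms, on the scales and on MRI, in a trial of 20 per arm where a few exclusions carry weight.

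**Working it through.** **1. The plan's own figure.** Sample size gives 16 per group and 20% dropout: 16 / (1 - 0.20) = 20 per group. This reproduces the stated 20. The planned loss is therefore 20 - 16 = 4 per arm, or 8 of the 40 patients, leaving 16 v 16.

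**2. Is the list a rule for analysis, or only for stopping treatment?** The schedule table and Outcome measures place the post-treatment scan at week 2, when the course ends. An incomplete week-2 scan cannot be a reason to stop treatment, so at least that clause excludes patients from analysis. The deletion option in the analysis section does so as well.

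**3. Do the two sections agree?** One takes out patients who withdraw or fall short. The other may impute values for patients who stop or deviate. Both cannot apply to the same patient, and nothing says which prevails.

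**4. Possible size.** Inputs: 20 per arm from the document. Assumed: no true effect, a normally distributed outcome with higher values better, removal from the lower end, and the split between arms. If the lowest fraction q is removed, the arm mean rises by φ(z_q) / (1 - q) SD:

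- q = 0.20: 0.280 / 0.80 = 0.350
- q = 0.10: 0.1755 / 0.90 = 0.195

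The bias is the acupuncture shift minus the control shift. It halves if the tendency to be removed correlates 0.5 with outcome. False-positive rates come from 20,000 simulated trials per row (two-sided t-test at 0.05; the document does not state sidedness).

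| Removed of 20, acupuncture v control | Bias, full link (SD) | Bias, correlation 0.5 (SD) | False-positive rate, full link | False-positive rate, correlation 0.5 |
|---|---|---|---|---|
| 4 v 0 | +0.350 | +0.175 | 0.204 | 0.085 |
| 4 v 2 | +0.155 | +0.078 | 0.115 | 0.064 |
| 4 v 4 | 0 | 0 | 0.100 | 0.059 |
| 2 v 4 | -0.155 | -0.078 | 0.120 | 0.062 |
| 0 v 4 | -0.350 | -0.175 | 0.193 | 0.081 |

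If removal is unrelated to outcome, there is no bias and the rate stays at 0.049 to 0.052. In the 4 v 4 row the means are unbiased, but under a full link the t-test still rejects too often, because cutting off one tail shrinks the spread it relies on.

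The mean shifts simulated with exactly 4 of 20 removed are slightly smaller than the formula gives (+0.335 and -0.330 at full link).

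**The case against.** A reader might infer that these rules favour acupuncture: only that arm can miss needling sessions or react to needles, so its poor responders leave while similar controls stay. The document does not support that as a conclusion. The removal rules are worded alike for both arms, so a control who worsens is removed too. These are patients within two weeks of a stroke, and worsening can occur in either arm. The word *tasks* is never defined as needling sessions and could cover scans, scales or basic treatment. The 20% dropout is applied to every group, so 20% v 0% is not the plan's expectation. A lean towards acupuncture is plausible and no more.

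A reader might also infer that imputation breaks the randomised comparison. It does not: it keeps the patient in the allocated arm. Nor does the article say that observed values would be overwritten. The faults are the deletion option, its trigger and the open choice.

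It is also fair to say that a condensed article may leave named analysis sets to a statistical analysis plan, and that removal can be read in part as ending participation. That does not answer the point. The article states an exclusion rule and a deletion option, and a later plan could cure them only by departing from them.

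Finally, the SD figures suit a scale with a clear better direction. For most of the MRI indices the article defines no worse direction, so the figures do not carry over directly to the primary outcome.

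**Conclusion.** The point stands as a stated rule that can bias the randomised comparison, with direction and size unknown. Removal depends on events after allocation that are related to outcome or treatment, deletion is allowed for anyone who stops or deviates, and the two sections are not reconciled. Up to 8 of 40 patients could be affected if losses match the planned 20%.

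In the illustration the bias runs from +0.35 SD to -0.35 SD, passing through zero when removal is equal. It rests on assumed splits between arms and an assumed link between removal and outcome, so the 0.35 SD figure is an extreme case and not a forecast. The remedy should be in place before week-2 data are lost, because measurements never taken cannot be recovered.

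**What to change.** 1. Reword Removed criteria so that it separates stopping study treatment from exclusion from analysis. The clinical decisions themselves stay as they are.
2. Seek the already scheduled week-2 scales and MRI in every randomised patient where consent and condition allow, whatever the number of sessions received.
3. Make the primary comparison between arms all randomised patients in their allocated arm, using observed values regardless of completion.
4. Delete listwise deletion for patients who stop or deviate. Use one prespecified multiple imputation method, and only for values that are truly missing.
5. Where voxel-wise MRI maps are missing, analyse all available scans by allocated arm and report the number missing and the reasons by arm. Some risk of bias remains for these maps, and this reporting makes it visible.
6. Define *tasks*, and report the set with at least 50% completion as a sensitivity analysis only.

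The cost is an amendment, some dilution of the estimate because patients with little treatment stay in, and effort to obtain week-2 data from those who stop. A scan will not be feasible in every patient who has worsened.

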### Randomization and blinding

An independent researcher will be responsible for generating random numbers and sealed in opaque envelope. After subjects agree to participate in this study, they will randomly obtain an assigned serial number. The identification cord and basic information about each enrolled patient will be recorded on the case report form. Indicator assessors will be not aware of specific subgroups. Information exchange between patients will be not allowed. An independent researcher will perform data management and statistical analysis tasks.

### Interventions

All patients will receive the conventional basic medications which refer to the Chinese guidelines for diagnosis and treatment of acute ischemic stroke2018 (7). All of these medications will be individualized to control blood pressure, blood sugar and lipid, and prevent platelet aggregation.

The difference is that the XNKQ group will receive 30 min of acupuncture treatment. We will use stainless steel disposable acupuncture needles (size 0.25 mm × 40 mm or 0.30 mm × 75 mm) (Changchun Aikang Medical Instrument Factory) for the treatment. All acupuncture therapists have more than 5 years of clinical experience and have uniform training to ensure that the treatments will be administered consistently.

### Acupuncture group

Acupoints of XNKQ acupuncture included bilateral PC6, DU26, and affected side SP6. Patients will be in the supine position. Acupoints will be sterilized with 75% alcohol before acupuncture. The first acupuncture point to be needled will be PC6, then the needle body will be rotated to stimulate the acupoints with a speed of 40-60/min and a rotation angle of more than 180°. The second will be DU26, the needle body will be rotated 360° and fixed to the skin, and moved to stimulate the acupoint until the eye is moist or weeping. Finally, SP6 will be stimulated until the leg twitches 3 times.

Depending on each patient’s tolerance level, the therapist adjusts the acupuncture strength until the patient achieves “deqi” without significant pain. Leave the needle in place for 30 min per treatment. Acupuncture 6 times per week for 2 weeks for a total of 12 times.

### Non-acupuncture group

In the non-acupuncture group, patients will receive the same basic treatments as the acupuncture group except for acupuncture.

### Healthy group

The healthy group will not receive any interventions.

### Sample size

This study focuses on MRI data. The sample size was calculated based on similar previous studies. Through reading the research literature on the mechanism of the functional effects of acupuncture on the brain, we found that the acute phase of stroke is generally characterized by an acute condition and poor compliance. Desmond et al. (8) showed that when analyzing functional MRI data with a free threshold of 0.05, it is probably necessary to include at least 12 subjects to achieve an activation efficacy of 80% or more at the single voxel level. Anecdotal evidence (9) suggests that fMRI studies typically involve 12 to 16 subjects per group. Therefore, we included 16 subjects in each group. Considering the high dropout rate, we set the 20% dropout rate and finally included 20 subjects per group. So, a total of 40 CIS patients and 20 healthy people will be enrolled.

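### The sample size rests on a single-voxel activation figure that does not describe the planned between-arm comparison, so 80% power for that comparison is not shown

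*Protocol article*

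**What the plan says.** All of the sizing is in the Sample size section of the protocol article, which says that the number was calculated from earlier similar studies. The steps are:

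- A cited methodological study, taken to show that "it is probably necessary to include at least 12 subjects to achieve an activation efficacy of 80% or more at the single voxel level". The threshold attached to this figure is 0.05.
- Custom in the field: "Anecdotal evidence (9) suggests that fMRI studies typically involve 12 to 16 subjects per group".
- The conclusion: "Therefore, we included 16 subjects in each group".
- Attrition: "we set the 20% dropout rate and finally included 20 subjects per group".

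Under Design and setting, "patients will be randomized into 2 groups in 1:1 ratio". Under Data collection and statistical analysis, the test is fixed: "Data will be analyzed with two independent samples *t*-tests", used for patients against healthy people before treatment and for acupuncture against no acupuncture after treatment. The criterion is "Statistical significance is defined as a *p* value of <0.05". The Abstract makes multimodal MRI the primary outcome. Primary outcomes lists ALFF and fALFF, ReHo, functional connectivity, grey matter by VBM, FA and CBF. Data acquisition describes resting-state scanning.

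**The concern.** The borrowed figure and the planned comparison differ in three ways.

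- **Quantity.** The figure concerns activation. The trial scans at rest and plans no task. VBM, FA and CBF are not BOLD measures at all.
- **Contrast.** The randomised question is a difference between two independent arms. The text does not say whether the cited 12 are one group, each of two groups, or a total.
- **Scope.** The figure is for one voxel at 0.05. The trial analyses several indices as brain images.

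No effect size or standard deviation is given, so nothing carries the cited 80% over to this trial. The step from 12 to 16 rests on custom alone.

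What is at stake is how a null result is read. The Discussion expects the results to support a mechanism and later clinical promotion. If the size is thought to be backed by an 80% figure, absence of a significant between-arm difference may be taken as absence of an effect, although a moderate effect would often be missed.

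**Working it through.** **Inputs from the protocol article.** 12 subjects, 80%, threshold 0.05; 16 evaluable per group; 20% dropout; 20 enrolled per group (Sample size). 1:1 allocation (Design and setting). Two-sample t-test and p < 0.05 (Data collection and statistical analysis). Not given: effect size, SD, sidedness, and what kind of sample the 12 are. Two-sided tests are assumed below.

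**Step 1: the plan's own arithmetic.** 16 / (1 − 0.20) = 20 per group, and 2 × 20 = 40 patients. This reproduces. The 12 and the 16 can be neither reproduced nor refuted, because no effect size is stated.

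**Step 2: what effect would the cited figure imply?** Power is P(T > t_crit), where T is noncentral t with noncentrality λ; the opposite tail is negligible. Let d be the standardised effect.

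- *Assumption A, 12 as one sample:* λ = d√12, df = 11, t_crit = 2.201. Power of 80% needs λ = 3.078, so d = 3.078 / 3.464 = 0.89.
- *Assumption B, 12 per group in a two-group test:* λ = d√(12/2), df = 22, t_crit = 2.074. Power of 80% needs λ = 2.932, so d = 2.932 / 2.449 = 1.20.

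**Step 3: put that effect into the planned test.** With 16 per arm, λ = d√(16/2) = 2.828d, df = 30, t_crit = 2.042.

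| Reading of the cited 12 | d | λ | Power at two-sided 0.05 |
|---|---|---|---|
| A: one sample | 0.89 | 2.51 | 68% |
| B: per group | 1.20 | 3.39 | 91% |

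Under A the same d is carried from a one-sample effect to a between-arm difference, which is itself an assumption. The two readings lie on either side of 80%.

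**Step 4: a statement that needs no reading of the source.** Solve the two-sample power for d at 80% with 16 per arm:

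| Two-sided level | Status | t_crit (df 30) | Detectable d |
|---|---|---|---|
| 0.05 | stated in the protocol (sidedness assumed) | 2.042 | 1.02 |
| 0.05/7 | illustration: seven indices, counting ALFF and fALFF separately | 2.887 | 1.33 |
| 0.001 | illustration: a voxel-level threshold | 3.646 | 1.61 |

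For assumed effects at two-sided 0.05, 16 per arm gives 28% power at d = 0.5, 59% at d = 0.8 and 78% at d = 1.0.

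**Step 5: covariates.** Spending five degrees of freedom on age, gender, BMI, blood pressure and diabetes history moves the 68.2% of reading A to 67.6%. Any gain from reduced residual variance is not counted, as no figure for it is given.

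**The case against.** A reader might infer that the design promises 80% power and that 16 per arm fails to deliver it. The documents do not support that. The section never claims 80% for this trial: it reports a cited minimum, adds custom, and goes above the minimum. The shortfall to 68% appears only if the cited 12 are one sample, which the text does not say. The following sentence there speaks of subjects per group, and on that reading power is 91%. This objection stands: the power is not established, rather than shown to be too low.

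A reader might also take the stricter thresholds as proof of low power. Neither 0.05/7 nor 0.001 is in the protocol, which states only p < 0.05. They serve as illustrations of direction and rough size, and no more.

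It can further be said that no calculation is wrong, and that the section is open about resting on precedent. Both are fair: the dropout step is correct, and the fault lies in the justification. But the section presents its number as calculated and offers the single-voxel 80% as a reason for it. That reason does not fit the comparison to be made. This is a defect in what the article states, and does not depend on detail that may sit in a fuller document.

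**Conclusion.** The point holds in limited form. The only power figure behind 16 per group describes activation at one voxel and is not tied to the between-arm t-tests on the primary MRI indices. Power for the randomised comparison is therefore undetermined: 68% or 91% at two-sided 0.05, depending on which assumption is made about the cited 12. The firm result is that 16 evaluable patients per arm detect about 1.02 SD with 80% power, for one measure, at an uncorrected two-sided 0.05, by a plain two-sample t-test with equal arms. It is not shown that the trial is underpowered for its true effect, which the documents do not specify.

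**What to change.** Keep 20 enrolled and 16 evaluable per group. In Sample size, remove the single-voxel 80% as the basis and write, for example:

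> Sixteen evaluable patients per arm give 80% power for a between-arm difference of about 1.02 SD in a single MRI measure at an uncorrected two-sided 0.05. Any correction for several indices or voxels raises the detectable difference (for illustration, about 1.3 SD at 0.05/7 and 1.6 SD at 0.001), so a null result does not exclude smaller effects.

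The precedent of 12 to 16 per group can stay as a feasibility argument, labelled as such. The new text should not mention one prespecified endpoint or a gain from baseline adjustment unless the protocol also adopts them. At present it names no single MRI endpoint, and its covariate list does not include the baseline MRI value.

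The cost is a change of wording, with no effect on enrolment or conduct. The downside is that the stated figure looks less favourable than the one it replaces.
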